## Abstract

**Trial registration:**

ClinicalTrials.gov NCT06093646

## Introduction

In 2014, the World Health Organisation (WHO) declared the 2014–2016 West African Ebola outbreak as a “public health emergency of international concern”, an epidemic that eventually engulfed three West African countries of Guinea, Sierra Leone, and Liberia, infected 28,616 persons, led to 11,310 deaths and left over 10,000 survivors [1]. Ebola Virus Disease (EVD) is now considered a threat to public health in the heavily populated regions of east, central and west Africa where since 1976 at least 35 EVD outbreaks have been reported [2]. To-date, Uganda has had 7 Ebola outbreaks with the most recent having occurred between 20^th^ September 2022 to the 11^th^ of January 2023, affected 9 districts (Mubende district was the epicentre), infected 164 persons (142 confirmed and 22 probable), led to 55 confirmed deaths, with 87 survivors and 4,000 contacts [3].

EVD is not only associated with a high mortality and physical morbidity, but also with mental health disorders. EVD related mental health disorders do not only affect EVD survivors, but also frontline health workers and volunteers and members of the affected communities [2,4–8]. Ebola survivors have been reported to develop the mental health problems of depression, anxiety, post-traumatic stress disorder (PTSD) and insomnia. These occur as a result of a number of factors including the trauma associated with the EVD illness experience (including the manner of evacuation from home that involves destruction of personal effects to prevent transmission of disease, and the harrowing experience in the Ebola treatment unit), being infected with a highly fatal disease, loss of loved ones, rejection, isolation stigmatisation by the community, and possibly as a result of secondary central nervous system (CNS) viral invasion with recent evidence pointing towards clinical and imaging features indicative of meningoencephalitis and meningitis [2,4–8]. For healthcare workers, providing medical care for EVD infected patients is mentally very stressful due to treating very sick patients, the high mortality in the Ebola treatment units, extended work shift times, risk of infection, fear of infecting family members, witnessing the death of colleagues, and having to wear personal protective equipment (which is uncomfortable, impairs communication and performance of diagnostic and therapeutic procedures). These all contribute to predisposing frontline health workers and volunteers to anxiety, depression, PTSD, fatigue and social isolation [9,10]. For members of Ebola affected communities, loss of loved ones, having loved ones isolated in Ebola treatment units and isolation centres, rejection and stigmatisation, threatened violence and sometimes actual violence and economic and social disruption associated with community lockdowns all contribute to mental health disorders [5,10,11]. EVD associated mental health disorders if not treated have been reported to have a tendency to chronicity with Kelly et al., (2019) in a follow-up study of EVD survivors of the 1995 Ebola Outbreak in Kikwit, DRC reporting persistence of depressive and anxiety symptoms two decades after the outbreak [2].

Despite this demonstrated need, the implementation of community mental health services in EVD affected communities remains poor [12]. This has been attributed to a number of reasons that include: affected communities are often remote and suffer from chronic war conflict; health systems in many sub-Saharan African countries are fragile as demonstrated during the 2014–2016 West African Ebola outbreak where a 2015 World Bank report noted that at the time of the West African Ebola outbreak, the number of mental health workers (including psychiatrist) in the local population was as low as 1 in 6 million in Sierra Leone and 1 in 25,000 in Liberia [13]; a lack of prioritisation of mental health by international humanitarian donor agencies in preference for biomedical interventions [14,15]. Therefore, there is an urgent need to commit more resources to mental health care in vulnerable regions including developing novel approaches to addressing this mental health burden.

One endeavour in this direction is being undertaken by the Mental Health Focus Area of the Medical Research Council/Uganda Virus Research Institute and London School of Hygiene and Tropical Medicine, Uganda Research Unit (MRC/UVRI & LSHTM Uganda Research Unit) in partnership with the Ministry of Health of Uganda, entitled, *‘Proposal to address the medium- to long-term EBOLA associated psychological Distress and psychosocial problems in Mubende District in central Uganda (Ebola+D Project)’. The Ebola+D Study will* be undertaken in Mubende District in central Uganda (the epicentre of recent Uganda EVD outbreak). This protocol describes the process that will be employed to develop, and pilot test the Ebola+D mental health intervention model to address the mental health problems of the Ebola affected Mubende district.

### Mental health care in the Mubende district at the time of the 2022–2023 Ebola outbreak

Mubende district (population 720,000, with 42 public health care facilities; 1 regional referral hospital, 12 health centre III facilities and 29 health centre II facilities [16]) at the time of the Ebola outbreak had limited mental health services that primarily consisted of 1 mental health department at Mubende Regional Referral Hospital. The entire district mental health work force consisted of only 12 mental health workers (1 psychiatrist, 2 psychiatric clinical officers and 9 psychiatric nurses) all based at the regional referral hospital with no primary mental health services at the more than 42 public health facilities in the district (*[name], field coordinator of the Ebola MHPSS response- personal communication December 2022*). Following the Ebola outbreak in Mubende district on the 20^th^ September 2022, the Ministry of Health of Uganda, established an Ebola National Task Force that had as one of its sub-pillars the Ebola Mental Health and Psychosocial Support Services (MHPSS). The MHPSS sub-pillar outlined three objectives: i) enhance the capacity of health workers and community volunteers to offer mental health and psychosocial support, ii) extend mental health and psychosocial support services to various segments of the community including EVD survivors and members of the affected community, and iii) provide mental health and psychosocial support services specifically tailored for frontline health workers. In the immediate aftermath of the outbreak, Mubende district saw an influx of psychosocial workers who supported the district to address the immediate mental health and psychosocial effects of EVD. In preparation for the scale down of MHPSS, the Ministry of Health with support of partners trained 90 members of the Village Health Team (VHT; the first level of primary health care in the Uganda health system; 10 VHTs per sub-county) to provide continued mental health and psychosocial support to the district. However, no mechanism was put in place to provide continued support for the trained VHTs and for upward linkage of referrals to the Mental Health Department at Mubende Regional Referral Hospital.

### Ebola+D mental health intervention

To address the above identified gap, the Mental Health Focus Area of the MRC/UVRI & LSHTM Uganda Research Unit proposes to develop and pilot the Ebola+D mental health intervention model that would employ a collaborative stepped care approach modelled on the HIV + D mental health intervention (a depression integration model that has shown effectiveness against depression and anxiety disorder in adult HIV care in Uganda) [17] which was developed by the Mental Health Focus Area modelled on the MANAS mental health intervention that demonstrated effectiveness and cost-effectiveness in primary healthcare in India [18]. The development of the Ebola +D intervention will be guided by four principles: i) the intervention should address the health system challenges in the district (low mental health literacy in the community, and inadequate knowledge and skills of non-specialist primary health care workers to identify and support patients with mental health issues; severe shortage of mental health workers in the district; shortage of other cadres of health care workers; a poor referral system in the district) [19,20]; ii) use the best global practices hence the task-shifting approach of using supervised trained lay health workers to deliver low intensity psychological treatments [18,21,22]; iii) the selected clinical treatments should have been shown to be effective against the target mental disorders (depression, anxiety disorders and PTSD), hence the selection of the psychoeducation [23], the transdiagnostic Problem Solving Therapy (PST) [24], and the use of Selective-Serotonin Re-uptake Inhibitors (SSRIs) for depression, anxiety disorder and PTSD [25–27]), iv) and the intervention should be guided by the specific needs of the patient and aligned with the concepts of person-centred care [28]. The overall goal of the Ebola+D intervention will be recovery from the mental health disorders (depression, anxiety and PTSD). This will be guided by two rules: allocation of the clinical treatments based on decision rules defined by severity of symptoms and response; and planned reviews of response at regular intervals (monthly until remission). The locally validated Luganda (Luganda is the predominant local language spoken in central Uganda) or English version of the WHO- Self Report Questionnaire (SRQ-20) [29,30] will be used by the trained lay health workers (members of the Village Health Team) to screen members of the community for psychological distress. The SRQ-20 which was developed by the WHO specifically for low- and middle- income (LMIC) settings employs a yes/no answer format (which is amicable to lay health workers who often have low levels of literary) and is designed to detect non-specific psychological distress, including suicidality [29].

The Ebola +D mental health intervention will be implemented at 11 public health care facilities (health centre IIIs and IVs) in Mubende District. The intervention will be delivered by the health centre based medical team, in collaboration with members of the village health team (VHT), who constitutethe first level of the Ugandan health care system. At each facility, the intervention will be coordinated by a designated mental health contact person,either a general nurse or general clinician based at the health facility, and will be supported by mental health professionals from Mubende Regional Referral Hospital. The delivery team at each site will comprise two trained lay health workers (selected from the VHT), a supervisor (selected from the health centre staff), two clinicians from the health centre, and a visiting specialist mental health worker (psychiatric clinical officer or psychiatric nurse) affiliated with Mubende Regional Referral Hospital.

A health centre III is a key part of Uganda’s decentralised healthcare system, providing outpatient, maternal and child health, inpatient care, laboratory, and HIV/AIDS services at the sub-county level. Staffed by clinical officers, nurses, midwives, and lab technicians, it features a maternity ward, inpatient ward, outpatient department and a laboratory. It serves as a referral point for health centre II facilities and collaborates with Village Health Teams to promote public health and preventive care. A health centre IV in Uganda is a higher-level facility within decentralised health care system, serving as the sub-district’s main health unit. It provides comprehensive outpatient and inpatient care, including advanced maternal and child health services, emergency obstetric care, and minor surgical procedures. It acts as a referral point for health centre III facilities. It is staffed by a medical officer, clinical officers, nurses, midwives, laboratory technicians, and support staff.

### The Ebola ±D mental health intervention will involve 4 steps

Step 1 (Initiation of treatment): Patients with SRQ-20 scores of ≥6) (demonstrated 84% sensitivity and 93% specificity) [29] are advised about their scores and offered Psychoeducation (undertaken by a lay health worker, member of the VHT).

Step 2: (Management of moderate to severe cases): Patients who remain symptomatic at follow up (SRQ-20 score ≥6, after 4 weeks) despite Step 1. These will be offered Problem Solving Therapy (PST; minimum 4 sessions, maximum 8 sessions) (undertaken by a lay health worker, member of the VHT).

Step 3: (Monitoring outcomes): If after 6 sessions of PST, SRQ-20 scores are still 6 and above, complete PST sessions and add Selective Serotonin Re-Uptake Inhibitor (SSRI; such as Fluoxetine 20 mg/day for 6 months) (SSRI medication initiated by clinician).

Step 4: (Referral to Mental Health Specialist/ Clinician in charge of facility): If despite Step 3 there is no improvement (SRQ-20 scores 6 and above); or at initiation of treatment or during any phase of treatment, if someone is deemed to have a high suicide risk confirmed by the supervisor (contact general nurse or clinician), following a positive SRQ-20 item 16 (‘do you feel that you are a worthless person?’) or/and item 17 (‘has the thought of ending your life been in your mind?’) [29], then continue all existing treatment and refer to a specialised mental health worker (psychiatrist, psychiatric nurse or psychiatric clinical officer at Mubende Regional Referral Hospital).

To develop the Ebola+D mental health intervention, we shall employ the methodology developed by PREMIUM (Program for Effective Mental Health Interventions in Under-Resourced Health Systems) [31] where participatory, theory-informed approaches will be used. The Mental Health Focus Area of the MRC/UVRI & LSHTM Uganda Research Unit has previously employed this methodology to support the development of the HIV + D mental health intervention. This will involve the following: i) develop a Health Talk about the psychosocial and mental health problems associated with EVD to be delivered at the triage area where community members who have come to access health services at the public health care facilities are waiting (to increase mental health literacy, messages will be drawn from the WHO Psychological First Aid Manual) [32]; ii) will develop the message that will be given in the Psychoeducation Session (1^st^ step of care in the Ebola+D mental health intervention); iii) will undertake the local adaptation and translation of Problem Solving Therapy for Primary Care (PST-PC) treatment manual [33]; iv) will undertake the training and supervision of lay health workers and their supervisors; v) will undertake the training of clinicians in mhGAP guidelines (including use of SSRIs) [34].

### Steps in the development of the Ebola+D mental health intervention

The development of the Ebola+D mental health intervention was guided by prior experience of the Mental Health Research Team (which included psychologists, psychiatrists, social workers and health economists) who had participated in the HIV + D trial and in the initial psychosocial response to the Ebola epidermic in Mubende district. Through a series of meetings by the Mental Health Research team a number of factors were noted, namely: i) the lack of primary mental health services in the target district; ii) the severe shortage of mental health workers in the district; iii) the severe shortage of medical personnel in the primary health facilities; iv) the fact that the community was struggling to cope with the negative consequences of the Ebola epidermic which occurred right on the heels of the COVID-19 pandemic, the team thought that the community would benefit from problem solving training rather than behavioural activation which had earlier been successfully used in the HIV + D trial; and v) the fact that the HIV + D stepped care collaborative model had been able to successfully circumvent the above challenges in HIV care. We therefore opted to adapt the HIV + D mental health intervention into the local situation in Mubende district through the following five phases: i) adapt the HIV + D collaborative stepped care mental health intervention into primary health care in Mubende district to produce the Ebola+D mental health intervention; ii) to adapt and translate the Problem Solving Therapy for Primary Care (PST-PC) treatment manual [33] to the local rural situation in Mubende district; iii) a pilot study to evaluate the acceptability, feasibility and impact on mental health outcomes of the Ebola+D mental health intervention; iv) a health economics component to examine the costs of the Ebola + D mental health intervention from the providers’ perspective to determine how much it will cost for the health system to set up and operate the intervention at the health facility level.; and v) to explore the Ebola virus disease (EVD) associated negative beliefs and lived out experiences of affected members of the community.

Problem Solving therapy (PST) is a low intensity cognitive-behavioral intervention that focuses on training in adaptive problem-solving attitudes and skills [33]. A meta-analysis by Bell and D’Zurilla (2009) using controlled outcome studies on efficacy of PST for reducing depressive symptomatology found that PST was equally effective as other psychosocial therapies and medication treatments and significantly more effective than no treatment [35]. Zhang and colleagues (2018) in a systematic review and meta-analysis of clinical trials examining PST for patients with depression and/or anxiety in primary care reported PST’s effectiveness for primary care depression and/or anxiety [36]. Connolly and colleagues (2021) in a systematic review and meta-analysis to investigate the effectiveness of community-based mental health interventions by professionally trained, lay counsellors in low- and middle-income countries, observed that the use of professionally trained, lay counsellors to provide mental health interventions in low- and middle-income countries was associated with significant improvements in mental health symptoms across a range of settings [37]. In this project we shall adapt the Problem-Solving Therapy for Primary Care (PST-PC) treatment manual by Hegel and Areán (2011) for use to train lay health workers (members of the Village Health Team) in the rural situation of Mubende.

## Materials and methods

### Setting and design

A participatory, mixed-method study will be employed to achieve the study phases. The study will be conducted in Mubende district in central region of Uganda, 160 kilometres west of Kampala, the capital city of Uganda. The health system where the Ebola+D mental health intervention will be developed consists of a Mental Health Department at Mubende Regional Referral Hospital at the apex of a network of 42 public health facilities (1 regional referral hospital, 12 health centre IIIs and 29 health centre IIs) that primarily do not offer any mental health services apart from the regional referral hospital.

### Participants and procedure

#### 1) To adapt the HIV + D collaborative stepped care mental health intervention to produce the Ebola+D mental health intervention.

We shall employ the Theory of Change (ToC) based approach by De Silva and colleagues (2014) [38] to adapt the HIV + D mental health intervention to the post-Ebola primary health care situation in Mubende district in Uganda. This participatory methodology has previously been used in the Ugandan setting by this research team [39] and will be used to achieve the following: i) describe the proposed causal pathway to impact; ii) increase the chances of success due to its sensitivity to the local context, stakeholder involvement and hence promotion of stakeholder buy-in; iii) help identify barriers and strategies needed to implement the HIV + D mental health intervention in post-Ebola Mubende district so as to ensure full integration and the achievement of the ultimate goal of recovery from Ebola associated mental health problems (depression, anxiety and Post-traumatic stress disorder); and iv) identify possible outcome indicators of the intervention.

Iterative theory of change (ToC) workshops will be held with the different categories of stakeholders who can influence the implementation of the intervention. Through a process of participatory discussions, consensus will be sought on the programme’s desired impact of having the integration of the management of common mental health problems in public health care facilities in Mubende district, Uganda. Each group will develop a programme theory describing how the intervention is expected to unfold and attain the desired impact. Also, to be discussed are the different cadres who will deliver and support the different steps of care in the Ebola+D mental health integration model, how these will be implemented, the competencies required to perform these roles and responsibilities and how these will be acquired and maintained, and the monitoring of quality and fidelity of treatment.

A final workshop, bringing together all willing stakeholders will be conducted. Findings from the separate ToC workshops will be presented, and consensus will be made on the causal pathway to impact, the intervention and indicators, assumptions, and rationale for each point along the causal pathway, a ToC map will be developed.

#### 2) To adapt and translate the Problem Solving Therapy for Primary Care (PST-PC) treatment manual to the local rural situation in Mubende district.

To locally adapt the problem solving therapy for primary care (PST-PC) manual to the post-Ebola situation in rural Mubende district, we shall employ a methodology similar to that used by Chowdhary and others, (2016) [31] in India and most recently used by Kinyanda and colleagues (2020) [17] to adapt Behavioural Activation therapy to the local HIV care situation in Uganda.

The adaptation process will involve presenting the PST-PC manual to different categories of stakeholders at separate workshops. The first workshop with mental health professionals (psychiatrists, psychologists, social workers and psychiatric nurses) will review the original manual and adapt it for use by lay health workers in the Ugandan setting. At the second workshop, the locally adapted PST-PC manual will be used to train potential lay health workers (including members of the village health team, representatives of patient support groups and hospital ward attendants), with the feedback obtained during the workshop used to further refine the PST-PC manual. After incorporating the feedback from the second workshop, the PST-PC manual will translated into the local language (Luganda) by a bi-lingual psychologist.

#### 3) To evaluate the acceptability, feasibility, and impact on mental health outcomes of the Ebola+D mental health intervention.

At the study PHCFs, community members accessing mental health services will be screened using the WHO SRQ-20. Those meeting the eligibility criteria, including ‘significant psychological distress’ (SRQ-20 scores ≥6) [29], will be triaged into appropriate levels of mental health treatment within the Ebola+D intervention. The triage process will consider baseline SRQ-20 scores, a suicidality risk assessment (based on a positive response to SRQ-20 item 16: ‘Do you feel that you are a worthless person?’ or item 17: ‘Has the thought of ending your life been in your mind?’), and confirmation of high suicide risk by the Supervisor (**Fig 1**).

**Fig 1 pone.0329591.g001:**
[figure not shown]
Ebola+D study flowchart.

Eligibility criteria for participating in this study: i) Community member of Mubende district staying within the catchment area of the PHCF; ii) 18 years and above, iv) able to communicate in either English or Luganda (local language spoken in the study region and the language into which the questionnaires will be translated), v) has a WHO SRQ-20 score of 6 and above.

Exclusion criteria: i) unable to engage with the research process for any reason that may include sensory impairment or cognitive impairment.

The study aims to enrol at least 100 respondents with psychological distress (SRQ-20 score ≥ 6) from each of the 11 participating PHCFs. Enrolled respondents will be provided with PST at bi-weekly sessions. Monthly assessments will be undertaken to monitor their level of psychological distress using the SRQ-20 until psychological distress scores have fallen to less than 6. A patient will be declared in remission if after completing their prescribed therapy (PST or medication) they remain symptom free (SRQ-20 scores of less than 6) on two occasions one month apart. A full complement of supporting and resource materials including clinic posters, health worker aide-memoire, and patient and care-giver resource materials will be developed and evaluated. The reporting of the trial will be in accordance with the SPIRIT guidelines for interventional trials [40] (S1 File).

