### Sample size and power calculations

The study will be longitudinal, with participants followed over a 12-month period. Psychological distress will be assessed using the SRQ-20, with a score of 6 or higher indicating distress. The primary outcome of interest will be remission of distress, defined as an SRQ-20 score below 6. All participants enrolled at baseline will have a level of distress. The intervention is hypothesised to reduce distress prevalence by at least 25%.

Given the longitudinal design and the use of clinic-based interventions, clustering effects will be accounted for by applying a design effect of 1.2, which reflects improved clustering control. Statistical parameters will include a confidence level of 95%. The total sample size will be fixed at 1,000 participants, requiring adjustments to the effective sample size to account for clustering.

The power calculation will be performed using a z-test for two proportions to compare the baseline and post-intervention prevalence of distress.

Using the assumed 25% absolute reduction in distress prevalence, the adjusted effective sample size of 1,000 participants, and a two-tailed significance level of 0.05, the estimated power of the study is calculated to be 94.5%.

Given the 12-month follow-up period and the community-based nature of the intervention, we anticipate an attrition rate of approximately 15%, based on evidence from similar longitudinal studies in rural Ugandan settings. Despite the anticipated attrition, the study will maintain the recruitment target at 1,000 participants, acknowledging that some loss to follow-up is expected. The analysis will account for missing data through multiple imputation techniques and sensitivity analyses to ensure that the study maintains sufficient power and validity to detect the hypothesized effect size.

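### The protocol sets two incompatible enrolment targets: at least 100 at each of 11 facilities (1,100 or more) and a total fixed at 1,000

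*Protocol article*

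**What the plan says.** Under Participants and procedure, item 3 (acceptability, feasibility and impact), the article sets a facility-level aim: "The study aims to enrol at least 100 respondents with psychological distress" (an SRQ-20 score of 6 or more) "from each of the 11 participating PHCFs". The number of facilities is confirmed in the section describing the intervention: "The Ebola +D mental health intervention will be implemented at 11 public health care facilities".

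Under Sample size and power calculations, the article gives an overall figure: "The total sample size will be fixed at 1,000 participants". It allows for clustering by "applying a design effect of 1.2". It expects about 15% attrition over 12 months but does not raise enrolment to cover it: "the study will maintain the recruitment target at 1,000 participants". The power statement in that section then uses 1,000 again, this time as the effective sample size after adjustment.

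No sentence links the facility aim to the overall figure. The number 1,100 does not appear, and 1,000 is not described as a minimum.

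**The concern.** Both statements describe how many people with an SRQ-20 score of 6 or more will be enrolled, and they give different answers. A facility team working to the first continues until it has at least 100. A coordinator working to the second closes enrolment at 1,000 overall. The article does not say which rule prevails.

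What is at stake is the closing point of recruitment and the denominator that the study will be held to. Stopping at 1,000 misses the facility aim somewhere, and enrolling 100 everywhere exceeds a total described as fixed. Either outcome would read as a departure from the published protocol.

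**Working it through.** **Inputs, all from the article**
- Facilities: 11 (stated in the intervention section and in item 3 of Participants and procedure).
- Minimum per facility: 100 (item 3).
- Fixed total and recruitment target: 1,000 (Sample size and power calculations).
- Attrition: about 15%. Design effect: 1.2 (same section).
- Effect: distress falls by 25 percentage points. Everyone is distressed at enrolment, so this is 100% to 75%. Two-sided alpha is 0.05, with a z-test for two proportions (same section).

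**Step 1: does the facility aim reproduce the stated total?**
- 11 × 100 = 1,100, against 1,000.
- Difference: 1,100 − 1,000 = 100, and 100 / 1,000 = 10%.
- In the other direction, 1,000 / 11 = 90.9 per facility. An average below 100 means that at least one facility is below 100.

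**Step 2: does a stated adjustment link the two figures?**
- 1,000 inflated for attrition: 1,000 / 0.85 = 1,176.5, rounded up to 1,177. Not 1,100.
- 1,100 reduced by attrition: 1,100 × 0.85 = 935. Not 1,000.
- 1,000 inflated by the design effect: 1,000 × 1.2 = 1,200. Not 1,100.
- 1,100 deflated by the design effect: 1,100 / 1.2 = 916.7. Not 1,000.
- Ten facilities at 100 would give exactly 1,000, but the article says 11 in both places.

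No adjustment in the article reconciles them.

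**Step 3: what effective sample size follows from each total?**

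| Enrolled | Divided by design effect 1.2 |
|---|---|
| 1,000 | 833 |
| 1,100 | 917 |
| 1,200 | 1,000 |

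An effective size of 1,000 at a design effect of 1.2 would need 1,200 enrolled, which matches neither target.

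**Step 4: does the gap matter for power?**

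With n per time point, p1 = 1.00, p2 = 0.75 and pooled p = 0.875, power = Φ(z), where

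z = [0.25 − 1.96 × √(2 × 0.875 × 0.125 / n)] / √[(1.00 × 0 + 0.75 × 0.25) / n].

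Take the least favourable size that 1,000 enrolled can give on the stated inputs. Losing 15% leaves 850, and 850 / 1.2 = 708. Then

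z = [0.25 − 1.96 × 0.01758] / 0.01627 = 0.2155 / 0.01627 ≈ 13.2,

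so power is above 99.9%. It can only be higher at 833 or 917. The article's own 94.5% is not reproduced from its stated inputs at 1,000, 850, 833 or 708 per time point. That is a separate matter and does not bear on which enrolment target governs.

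**Step 5: does it matter for precision?**

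The article states no precision figure, so this is an illustration that assumes 75% remain distressed. The 95% half-width is 1.96 × √(0.1875 / n): 2.9 points at n = 833 and 2.8 points at n = 917. The ratio is √1.1, about 5%.

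**The case against.** The strongest defence is that the facility figure is only an aim, while the sample size section is the formal statement. This softens the conflict but does not remove it, because that section calls 1,000 the recruitment target as well as the fixed total. Both sentences are therefore enrolment goals for the same people. Nor can 1,000 be read as a floor, since the total is described as fixed. The brevity of a journal article is no answer either: nothing is missing here, and two current statements disagree.

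The case for limiting the consequences is sound, and three stronger readings should be set aside.
- A reader might infer that the study could be underpowered. Power for the hypothesised reduction is above 99.9% at either total.
- A reader might infer that the design effect and every precision figure shift with this number. The design effect of 1.2 is assumed, not derived from cluster size, so 91 or 100 per facility leaves it as stated. The article gives neither an attrition-adjusted size nor a precision figure. Multiple imputation is also planned, so a count of completers is not its analysis size.
- A reader might infer that fast facilities will fill the total and leave slow ones under-represented. The article does not describe competitive enrolment, and a facility minimum, if honoured, works against it. Only the shortfall in the average is established.

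**Conclusion.** The contradiction stands. The two targets differ by at least 100 participants (10% of the fixed total), and no adjustment in the article connects them. The conclusion rests only on the article's own counts: 11 facilities, at least 100 at each, and 1,000 overall.

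The practical effect is modest. The conflict concerns which target governs and when recruitment closes, not whether the study can detect the hypothesised effect. The article gives no ground for preferring one figure: the facility aim is explicit and the facility count appears twice, while 1,000 is stated both as the fixed total and as the recruitment target and is the basis for the power statement. Changing the total alone would not make the section consistent, because the effective size of 1,000 fits neither target at a design effect of 1.2.

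**What to change.** State one governing target and say when recruitment closes. Two versions are consistent, and the choice is the sponsor's.
- **The total governs.** Keep 1,000 and restate the facility aim as about 91 on average. Effective size at the stated design effect: about 833. This changes text only.
- **The facility aim governs.** Keep at least 100 at each of 11 facilities and restate the total and recruitment target as at least 1,100. Effective size: about 917. Relative to the sample size section, this means 100 more participants to recruit, treat and follow for 12 months.

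In either case, replace the effective sample size of 1,000 with the matching figure and restate the power calculation from it. The edits are a sentence in item 3 of Participants and procedure or in the sample size section, plus the effective size and power lines.
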